**Design::**

This is a multicenter, central-randomized, controlled, double-blind, noninferiority, 2 factors and 3 levels orthogonal clinical trial. A total of 100 participants with ischemic stroke aged from 40 to 80 were randomized into experimental group and control group, the experimental group was divided into 9 groups (A1-A9) according to different factors or levels, and each group have 10 participants. The whole study period is 17 days, including 1 week for baseline observation, 3 days treatment and observation, and 1 week follow-up. Primary outcome is the fMRI based on blood oxygenation level dependent. Secondary outcomes included National Institute of Health Stroke Scale, Modified Barthel Index, Brunnstrom stroke recovery, stroke Chinese medicine symptom. Clinical assessments will be evaluated at before and the 0 hour, 24 hours, 36 hours after treatment, and 1 week follow-up. The primary outcome of the postacupuncture effect were investigated by paired T-test, and the continuous outcome variables will be analyzed with univariate repetitive measurement deviation analysis. Adverse events will be noted and recorded for the safety evaluation.

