### Study design

2.1

This is a multicenter, central-randomized, controlled, double-blind, noninferiority, 2 factors and 3 levels orthogonal trial. A total of 100 participants were randomized into experimental group and control group, the experimental group was divided into 9 groups (A1-A9) according to different factors or levels, and each group have 10 participants. This trial recruited participants from 3 sub centers: the First Affiliated Hospital of Yunnan University of Traditional Chinese Medicine (TCM), the Affiliated Hospital of Yunnan University and Kunming Yan’an Hospital, recruitment advertisements will be placed on the network and bulletin boards. Eligible participants will have an equal chance of being allocated randomly to experimental group or control group.

The whole study period is 17 days, including 1 week for baseline observation, 3 days treatment and observation, and 1 week follow-up. Participants will be monitored cerebral functional connectivity changes by fMRI before and the 0 hour, 24 hours, 36 hours after treatment, and scales was used to evaluate the clinical efficacy during the treatment and follow-up period. Figure 1 shows a flowchart of the study.

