### Randomization, allocation concealment, and blinding

2.6

After recruitment, a statistician who is not taking part in the clinical intervention will use SPSS 25.0 (IBM, Chicago, IL) to generate a random allocation sequence, the eligible participants who meet the inclusion criteria will be randomly distributed to experimental group and control group with proportion of 9:1. Participants in the experimental group will random reassignment to A1-A9 via the central randomization system by statistician from each sub centers. Each subject will received a unique random ID. The allocation concealment procedure will not be exposed until the clinical trial is finished completely. The baseline assessment and questionnaire administration was conducted by researcher A. Assessments and measurements of the participants will be carried out before and after the treatments by researcher B. Researcher C as image analyst will processed and analyzed the fMRI images to observed the cerebral functional connectivity changes. A licensed acupuncture researcher who has worked for more than 10 years will conduct acupuncture intervention on participants, whereas all subjects will deprived from knowing something about the pattern of treatment.

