#### Experimental group

2.7.1

The acupoint prescription was “Shenyang Tongdu” acupuncture according to TCM theory and clinical experience. Acupoints are including DU14 (Dazhui), DU9 (Zhiyang) and DU4 (Mingmen). The experimental group adopted 2 factors and 3 levels orthogonal trial, the 2 factors of time and frequency include 3 levels of different parameters, and the intersection of different parameters constituted 9 groups (A1-A9). Time refers to the operating time, including 60 seconds, 120 seconds, 180 seconds. Frequency refers to the twists per minute without lifting, including 120 bpm, 180 bpm, 240 bpm, the range of twirling manipulations is about 180°. Participants only received acupuncture once, and the rest of the time was observation and follow-up period. Specific parameters of each experimental group are shown in Figure 2.

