### Statistical analysis

2.10

The BOLD-fMRI data processing and analysis is based on the DPABI 4.3 of Matalab platform. Including removal of the first 10 time points, time correction, head movement correction (eliminating the data of head movement translation >2 mm or rotation shift >2°). Regression white matter and cerebrospinal fluid signals were used to remove interference. Spatial normalization, spatial smoothing, and linear drift removal were performed. If the data met normal distribution, the image characteristics of the postacupuncture effect were investigated by paired T-test.

Firstly, a gray matter mask was made for the subjects in this study, and the differences before acupuncture were found by paired T-test (*P* < .05). The whole brain gray matter mask was used to subtract the areas with significant differences before acupuncture, so as to exclude the pixels with significant differences at baseline. Paired T-test was used to investigate the changes of fALFF, ReHo, DC, and seed point FC before and after acupuncture in the intra-group comparison. Paired T-test was used to further find the differences in cerebral activity between groups compared with different stimulation quantity. The statistical results were corrected, if the threshold voxel level *P* < .01 and the cluster level *P* < .05, the difference was statistical significance.

Continuous outcome variables including NIHSS scores, MBI scores, Brunnstrom scores and stroke Chinese medicine symptom scores at before and the 0 hour, 24 hours, 36 hours after treatment, and 1 week follow-up will be analyzed with univariate repetitive measurement deviation analysis. Chi-Squared test will be used for comparison between groups.

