## Discussion

3

Ischemic stroke is a major chronic non-infectious disease that seriously endangers health, which is the main cause of persistent and acquired disability in adults worldwide.^[3,24]^ Numerous clinical studies and practices have shown that acupuncture is effective for stroke and less adverse reactions.^[25,26]^ However, the current studies mainly focus on the observation of the efficacy, the mechanism of acupuncture treatment for ischemic stroke has not been concluded. Therefore, we hope to obtain high-quality research data from this multicenter clinical trial, so as to provide reliable basis for future related studies.

Acupuncture manipulation is an important link in the process of acupuncture treatment and one of the key factors affecting the curative effect. As one of the basic acupuncture techniques, twisting manipulation is widely used in clinical. A large number of theoretical, basic and clinical studies have shown that different acupuncture stimulation have different effects.^[27,28]^ Using different twist stimulation, the treatment effect of the same disease is different, using the same twist stimulation in the treatment of different diseases, the therapeutic effect is not the same.^[29,30]^ This study can determine which time or frequency is most important in the course of acupuncture treatment for ischemic stroke. Whether there are differences in cerebral functional connections over time and frequency. The optimal combination of stimulation time and frequency can be obtained by observing the changes of cerebral functional connections through orthogonal trial design.

The purpose of this study was to evaluate the central mechanism of acupuncture stimulation quantity using time and frequency as control conditions. Our study protocol was designed through extensive discussion of several previous relevant studies.^[31–33]^ We try to minimize any biases that might affect the results of the study. By observing the changes of cerebral functional connectivity based on fMRI, this study will provide reasonable stimulation parameters and strong mechanism evidence of cerebral central network for the use of acupuncture for ischemic stroke.

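### The stated primary fMRI tests contain no time, frequency or interaction term, so they do not directly support the conclusions promised from the 3x3 design

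*Protocol article*

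**What the plan says.** Section 2.7.1 of the protocol article states the design: "The experimental group adopted 2 factors and 3 levels orthogonal trial". Operating time is 60, 120 or 180 seconds and twisting frequency is 120, 180 or 240 per minute. Section 2.1 adds that "the experimental group was divided into 9 groups (A1-A9) according to different factors or levels, and each group have 10 participants". All nine combinations are used, so this is a full 3x3 factorial.

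The Discussion (section 3) says what the design is for: "This study can determine which time or frequency is most important in the course of acupuncture treatment for ischemic stroke". It also expects the design to show whether connectivity differs over time and frequency, and to yield the optimal combination of the two.

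The primary analysis is named twice. The Abstract (Design) says: "The primary outcome of the postacupuncture effect were investigated by paired T-test". Section 2.10 repeats it for comparisons within a group ("Paired T-test was used to investigate the changes of fALFF, ReHo, DC, and seed point FC before and after acupuncture") and then names the paired t-test again for comparisons between groups given different stimulation quantities. The threshold is voxel P<.01 with cluster P<.05. The secondary scales get a repeated-measures analysis and a chi-squared test between groups. Neither manipulation time nor frequency appears as a factor in any of these analyses.

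**The concern.** Which factor matters most is a question about main effects. Which combination is best is a question about the nine cell means, and it depends on whether the factors interact. The stated tests estimate neither a main effect nor an interaction. A reader of the results would have to piece together an answer about time or frequency from separate group comparisons, with no stated rule for doing so.

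Two further features weaken the tests that are named:

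- **The within-group test is not a test of stimulation.** Patients are within 3 months of a first stroke and are rescanned at 0, 24 and 36 hours. Change inside one group therefore includes recovery and rescan variation as well as any effect of the manipulation.
- **The between-group test is the wrong form.** Section 2.6 randomises separate patients to A1-A9. A patient in one group has no natural partner in another, so a paired test has no defined pairs.

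At stake are the precision of the factor comparisons, and whether the Discussion's conclusions rest on a test that addresses them.

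**Working it through.** **Inputs from the protocol article.** N is 100 (section 2.1), the ratio is 9:1 (section 2.6), there are 10 patients per group (section 2.1), and there are two factors at three levels each (section 2.7.1).

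**Assumptions.** The article gives no SD, effect size or dropout rate. I set the SD of the change to 1, take differences of 0.5, 0.8 and 1.0 SD as a range, assume no dropout, and take tests as two-sided because sidedness is not stated.

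**Step 1: the plan's own figure.** 9 x 10 + 10 = 100, which agrees with 9:1. Each level of a factor occurs in three groups, so it has 3 x 10 = 30 patients.

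**Step 2: precision.** The variance of a difference of two means is 2 x SD²/n.

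- One pair of groups, 10 v 10: 2/10 = 0.200, SE = √0.200 = 0.447 SD.
- Two levels of one factor pooled over the other, 30 v 30: 2/30 = 0.067, SE = √0.067 = 0.258 SD.
- Ratio: 0.067/0.200 = 1/3.

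The pooled contrast is the average of three independent 10 v 10 contrasts: (3 x 0.200)/9 = 0.067. The gain comes from combining them, which section 2.10 does not say will be done. Pooling estimates one common effect only if the factors are additive.

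**Step 3: single-test power.** Noncentral t with noncentrality d/√(2/n), on 18 df (10 v 10) and 58 df (30 v 30).

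| Assumed difference d | Noncentrality, 10 v 10 | Noncentrality, 30 v 30 | Power at .05, 10 v 10 | Power at .05, 30 v 30 | Power at .01, 10 v 10 | Power at .01, 30 v 30 |
|---|---|---|---|---|---|---|
| 0.5 SD | 1.12 | 1.94 | 19% | 48% | 6% | 24% |
| 0.8 SD | 1.79 | 3.10 | 40% | 86% | 17% | 67% |
| 1.0 SD | 2.24 | 3.87 | 56% | 97% | 29% | 88% |

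Using the 90 - 9 = 81 error df of the full 3x3 model changes the 30 v 30 figures by less than one percentage point.

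**Step 4: the less favourable comparisons.**

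- *Omnibus main effect.* For a linear trend spanning 0.8 SD, the noncentrality is 30 x (0.4² + 0² + 0.4²) = 9.6. The 2-df F test (81 error df) then has 78% power at .05 and 56% at .01, below the 86% and 67% of the single contrast.
- *Extreme groups.* If both factors are additive and each spans 0.8 SD in the same direction, the two extreme groups differ by 0.8 + 0.8 = 1.6 SD. The noncentrality is 1.6/0.447 = 3.58, and 10 v 10 has 92% power at .05 and 75% at .01.

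**Step 5: design against test.** The 3x3 layout supports 2 df for time, 2 for frequency and 4 for their interaction. None of these 8 df is addressed by a test named in section 2.10.

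**The case against.** The strongest reply is that stimulation quantity is in fact compared. Section 2.10 does not stop at before/after tests; it adds a between-group step, loosely enough worded that it might cover pooled levels. Change common to all randomised groups cancels in such a contrast, so the recovery and rescan problem belongs to the within-group test alone. The best-combination aim is partly a matter of cell means, for which group comparisons are relevant, and Step 4 shows that extreme groups can be compared with good power. This is also a condensed article, and a fuller plan may hold a factorial model.

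Much of this stands, and it limits the point. A reader might infer that the trial's question goes untested, or that two thirds of its information is lost. The article does not support either: some stimulation differences are examined, and the one-third variance ratio is for one group pair against one pooled contrast under additivity. A reader might also infer that the investigators will judge stimulation effects by which groups reach significance. The article nowhere says so.

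Two parts of the reply do not stand. Pooling over levels is not stated, and sections 2.1 and 2.7.1 use the word group for A1-A9. Nor is this silence left for a fuller plan to fill: the article names the primary test in both the Abstract and section 2.10, and a factorial model elsewhere would conflict with it.

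**Conclusion.** The point holds as a mismatch between the declared design, the promised conclusions and the named primary tests. Those tests do not directly support a statement on which factor matters most, or on the best combination. Where they do compare stimulation groups, the paired form does not fit independent patients.

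The threefold variance ratio follows from the group sizes but needs additivity for the pooled contrast to be the right target; with a strong interaction the gain is smaller. The powers rest on assumed effect sizes and no dropout. They describe one test at a fixed level, and neither set is the trial's power under the voxel and cluster rule. The mismatch should be corrected before analysis because the main conclusions depend on it.

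**What to change.** In section 2.10 and the Abstract, replace the stated between-group test as follows.

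- For each fMRI metric (fALFF, ReHo, DC, seed-point FC) and each post-treatment scan, make the main between-group analysis a voxelwise two-way model in A1-A9. Include time, frequency and time x frequency, adjust for the baseline map value and centre, and keep the existing voxel and cluster correction.
- Report the interaction and the nine cell means before naming a best combination.
- Use independent-sample or model-based contrasts, not paired tests, for any follow-up comparison of groups.
- Keep the within-group before/after tests as descriptive.

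The cost is a change of wording and of model; no patient or scan is added. The downside is that level averages are hard to interpret if the interaction is large, which is why the interaction and cell means must be reported with them. The change does not settle which of the four metrics and three post-treatment scans (4 x 3 = 12 analyses) carries the main conclusion.

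### The plan assigns a paired t-test to fMRI differences between the stimulation-quantity arms A1-A9, which contain different, unmatched participants, so no valid pairs exist

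*Protocol article*

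**What the plan says.** The Statistical analysis section (2.10) of the protocol article uses the paired t-test at three steps of the group-level fMRI analysis.

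1. **Baseline mask.** "the differences before acupuncture were found by paired T-test", at P<.05. Areas that differ are then removed from the grey-matter mask. The sentence does not say what is compared with what.
2. **Within-arm change.** The paired test is applied to fALFF, ReHo, DC and seed-point FC "before and after acupuncture in the intra-group comparison".
3. **Between-arm contrast.** "Paired T-test was used to further find the differences in cerebral activity between groups compared with different stimulation quantity".

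No two-sample test, ANOVA or factorial model is named for the fMRI outcome, and no separate fMRI test is named for experimental versus control. Significance requires voxel level P<.01 and cluster level P<.05.

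On the design, Study design (2.1) states "A total of 100 participants were randomized into experimental group and control group" and "the experimental group was divided into 9 groups (A1-A9) according to different factors or levels, and each group have 10 participants". Under Randomization (2.6), participants "will be randomly distributed to experimental group and control group with proportion of 9:1", and then "Participants in the experimental group will random reassignment to A1-A9 via the central randomization system". Under Interventions (2.7.1 and 2.7.2), each participant has a single acupuncture session. Neither crossover nor matching of participants between arms is described.

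**The concern.** A paired t-test analyses differences within pairs that exist before the data are seen, such as the same person scanned twice or two people matched by design. Step 2 meets that condition and step 3 does not. Participant 1 in A1 has no link to participant 1 in A2 beyond a position in a list.

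The contrast matters. The Introduction makes the effect of different stimulation quantities on the brain network the primary objective. The Discussion expects the trial to identify the best combination of time and frequency. Both depend on comparing A1-A9 with one another on fMRI, and the paired test is the only fMRI test named for that.

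**Working it through.** **Arm sizes.** 9 arms × 10 + 10 controls = 100, and 9:1 of 100 is 90:10, so the stated numbers agree. The article gives no effect size, SD or power for fMRI. The differences used below (1 and 1.5 SD) are therefore assumptions, as is the scan loss. All test calculations are for one voxel at two-sided P<.01 and do not model the additional cluster criterion.

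**1. Why order matters.** With n = 10 per arm, the mean difference between two arms is the same however people are paired. The standard error is not. The variance of the pair differences is s₁² + s₂² − 2·cov, and cov is set entirely by which person is placed next to which. In 500 simulated 10 v 10 data sets with a true 1 SD difference and 200 random pairings of each, the central 95% of pairings typically (median over data sets) ran from P of about 0.007 to about 0.11. Identical data can therefore fall on either side of .01.

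**2. Degrees of freedom and critical value.**

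| Test | df | Critical t, P<.01 |
|---|---|---|
| Independent two-sample | 10 + 10 − 2 = 18 | 2.88 |
| Paired | 10 − 1 = 9 | 3.25 |

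**3. Power.** With arbitrary pairing there is no true correlation within pairs. The noncentrality is then the same for both tests, d·√(n/2) = d·√5, and only df and the critical value differ. From the noncentral t distribution:

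| Assumed difference d | Noncentrality | Independent, 18 df | Paired, 9 df |
|---|---|---|---|
| 1 SD | 2.24 | 29% | 23% |
| 1.5 SD | 3.35 | 68% | 56% |

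**4. Type I error.** In 100,000 simulated null data sets, rejection at .05 was about 5% for both the arbitrarily paired and the independent test.

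**5. Unequal arms.** Section 2.10 discards data with head movement above 2 mm or 2°, and sections 2.5.3 and 2.9 provide for dropouts. If each scan is usable with probability 0.9 (assumption), the number left per arm is Bin(10, 0.9). The chance that two arms end up equal is Σ P(k)² = 0.349² + 0.387² + 0.194² + 0.057² + 0.011² + … = 0.31. In the other 69% of cases, a paired test can run only by dropping usable scans from the larger arm, and nothing in the design says which.

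**The case against.** **Paired may be a slip for pairwise.** This is plausible. But the sentence immediately before uses the same term, correctly, for change within an arm. An analyst following the text would run the same procedure in both places. If it is a slip, the published wording still misstates the test.

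**Details belong in a statistical analysis plan that is not shown.** That would answer an omission. Here a specific test is stated for a specific contrast, and it does not fit the design.

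**Part of the primary analysis is sound.** This stands. The Abstract links the primary outcome to the post-acupuncture effect by paired t-test, and for before-versus-after change in the same people that is appropriate.

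**The numerical loss is moderate.** This also stands. The loss is 6 points of power at 1 SD and 12 at 1.5 SD, for assumed effects in a single voxel. These figures illustrate the cost and do not describe the trial's full voxel-and-cluster decision rule.

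A reader might infer three stronger things that the document does not support:

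- *That false positives are inflated.* Step 4 of the working shows that they are not.
- *That a paired test is prescribed across all ten arms.* The quoted sentence concerns groups differing in stimulation quantity, that is A1-A9. The control differs in acupoint prescription, and no fMRI test is named for that contrast.
- *That the baseline-mask step certainly has the same fault.* Its purpose, removing areas that differ at baseline, suggests that arms are compared, but the sentence does not say so.

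**Conclusion.** The test is wrong as written for the between-arm contrast among A1-A9, and it should be corrected before analysis because that contrast carries the stated objective. The conclusion rests on the design as described (individual randomisation, one session per person, no matching) and needs no assumed figure. The consequences are a P value that depends on arbitrary ordering, some loss of power, and forced discarding of usable scans when arms become unequal. The size of the last two depends on the assumed effect sizes and scan loss. The baseline-mask step shares the fault only if it compares arms, and the experimental-versus-control fMRI contrast currently has no named test.

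**What to change.** - **Within arms:** keep the paired t-test, and state that it is used only for before-versus-after change in the same participants.
- **Between arms at 0 h, 24 h and 36 h:** specify an independent-groups voxelwise model. The minimum is a two-sample test or ANOVA of change maps, with time and frequency as factors across A1-A9. An ANCOVA of the post-treatment map with each participant's own baseline map value as covariate is an acceptable alternative. State which independent-groups test applies to experimental versus control.
- **Baseline mask:** say what is compared. If it is arms, use a two-sample t-test or one-way ANOVA of the baseline maps. Change maps and baseline-adjusted ANCOVA cannot be used at this step, because no post-treatment map enters it.

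The cost is a few sentences of analysis wording. No extra participants, scans or data are needed, and the independent-groups model accepts unequal arm sizes.

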#### Dropout criteria

2.5.3

Participants who are unable to comply with this study, or who experience severe changes in their condition during treatment, will be dropped from the study.

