#### Secondary outcomes

2.8.2

National Institute of Health Stroke Scale (NIHSS)^[20]^ scores for neurological deficit, Modified Barthel Index (MBI)^[21]^ scores for activities of daily living, Brunnstrom stroke recovery Scale^[22]^ scores for limb muscle strength, stroke Chinese medicine symptom Scale^[23]^ scores for curative effects of stroke. These scales will be used to evaluate efficacy at before and the 0 hour, 24 hours, 36 hours after treatment, and 1 week follow-up period. Participants’ diary for their temperature, breathe, heart rate, blood pressure, drugs, adverse events (AE), and others during the research was recorded. All the dropouts and causes will be documented in case report form (CRF). The study schedule is shown in Figure 3.

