### Adverse events

2.9

Any possible AE related to acupuncture intervention that occur, including nausea, subcutaneous bleeding or hematoma, needle stuck or breakage, and pain will be checked and treated. Details of AE will be recorded in the CRF by the acupuncturist and security administrator. Severe AE will be reported to the Ethics Committee. Participants who are unwilling to persist with the treatment will be removed from the trial.

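### As standardly run, the repeated-measures ANOVA named for the secondary scales drops every patient with one missing score, including the scores already collected

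*Protocol article*

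**What the plan says.** Section 2.8.2 of the protocol article names four secondary scales (NIHSS, Modified Barthel Index, Brunnstrom and the Chinese medicine symptom scale). They are used to "evaluate efficacy at before and the 0 hour, 24 hours, 36 hours after treatment, and 1 week follow-up period", which makes five scores per patient and scale. Section 2.10 fixes the method: the scores at these times, up to "36 hours after treatment, and 1 week follow-up will be analyzed with univariate repetitive measurement deviation analysis".

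The design is small per arm. Section 2.1 states that "A total of 100 participants were randomized into experimental group and control group", with nine experimental arms, and "each group have 10 participants". Section 2.6 gives the allocation as "randomly distributed to experimental group and control group with proportion of 9:1".

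The article expects incomplete patients. Section 2.5.3 says that those who cannot comply, or "who experience severe changes in their condition during treatment, will be dropped from the study". Section 2.9 adds: "Participants who are unwilling to persist with the treatment will be removed from the trial". Section 2.8.2 has dropouts and their causes entered in the case report form. The article gives no expected dropout rate, does not mention imputation, and does not say that the model accepts incomplete records.

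**The concern.** This is about a method that the article names, not about a missing-data section that an unseen analysis plan might hold. In its usual wide-format form, a univariate repeated-measures ANOVA works on patients with all five scores. Three of the four post-treatment scores fall within 36 hours of a single session and the last comes about a week later, so a missed 1-week visit is a natural pattern of loss. Such a patient's 0-, 24- and 36-hour scores exist, yet they leave the analysis.

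Two things are at stake. One is precision in arms of 10. The other is selection: if patients who do worse early are less likely to return, those who remain look better than the arm did, even at 36 hours, where everyone was measured.

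**Working it through.** **Inputs from the article.** Five scale assessments (2.8.2); 10 arms of 10 (2.1, 2.6). Check of the stated total: 9 × 10 + 10 = 100, as stated. No dropout rate or SD is given, so every missing rate and SD below is an assumption.

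**Scores lost if only the 1-week visit is missed.** Let d of 100 patients miss it. Scores collected per scale = 500 − d; kept by complete rows = 5 × (100 − d); discarded = 4d; share = 4d / (500 − d).

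| d | collected | kept | discarded | share |
|---|---|---|---|---|
| 5 | 495 | 475 | 20 | 4.0% |
| 10 | 490 | 450 | 40 | 8.2% |
| 20 | 480 | 400 | 80 | 16.7% |

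**Sensitivity: independent loss m at each of the four post-treatment visits.** Complete share = (1 − m)^4. For m = 2%, 92.2 of 100 patients are complete and 30.8 of 492 collected scores (6.3%) are discarded. For m = 5%, the figures are 81.5 patients and 72.7 of 480 scores (15.2%). This pattern is less plausible, because it assumes equal loss immediately after needling and at 1 week.

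**Behaviour of the methods.** On simulated data (100 patients, five visits, 10 patients without the last score), a classical repeated-measures ANOVA routine refused the data as unbalanced. Complete rows kept 450 scores and a mixed model kept all 490. A long-format univariate fit with patient as a factor also kept 490.

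**Precision.** Smallest detectable difference between two single arms at one time point (80% power, two-sided 5%, normal approximation) = (1.96 + 0.84) × √(2/n). For n = 10: 2.80 × 0.447 = 1.25 SD. For n = 8: 2.80 × 0.500 = 1.40 SD.

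**Bias within an arm.** Assume a true mean change to 36 hours of −0.40 points and 1-week loss that is more likely after a poor change (logistic, slopes 0.5 and 1.0, giving 10.6% and 16.9% loss). With an SD of change of about 1.8, complete rows give −0.56 and −0.79 at 36 hours, shifts of 0.16 and 0.39 points. With a score SD of 3 and correlations of 0.7 to 0.9:

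- At 11 to 17% loss, complete rows give −0.50 to −0.96. The shift is 0.10 to 0.56 points; divided by 3, that is 0.03 to 0.19 SD.
- At 5% loss they give −0.45 to −0.59. The shift is 0.05 to 0.19 points, or 0.02 to 0.06 SD.

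If loss depends instead on the 36-hour score itself (about 14% lost), the completers' 36-hour mean shifts by about 0.16 SD. In the change-dependent scenarios, using all available data recovered −0.40.

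**Bias between arms.** Under the same loss mechanism in both arms (SD of change about 1.8), a true difference of zero stayed at 0.00. A true difference of −0.5 became −0.47 and −0.41, that is 0.03/0.5 = 6% and 0.09/0.5 = 18% too small. Across the SDs tried, the shrinkage was about 4 to 25%.

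**The case against.** The article never says that incomplete patients are deleted. Deletion is a property of the standard procedure, and the long-format fit above shows that a univariate model can keep incomplete rows. An unseen plan could also impute. This stands as a limit on the wording: it would be too strong to say that the method cannot use incomplete patients. But the article signals neither variant, and the unqualified name points to the standard procedure.

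A reader might infer that the trial's treatment comparisons will be inflated, since the within-arm change at 36 hours can look 40% too large (0.16/0.40) or nearly double. The documents do not support that. The percentage rests on a small assumed true change. It also describes change within one arm, whereas the trial compares stimulation levels and control, and that comparison is shrunk or unaffected when loss is similar across arms.

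A reader might also infer that 11 to 19% of patients will be lost, which is 1 − 0.97^4 to 1 − 0.95^4. That needs 3 to 5% independent loss at all four visits. The same 3 to 5% at the 1-week visit alone deletes only 3 to 5% of patients.

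Three further objections stand in part. The removal rules in 2.5.3 and 2.9 are tied to treatment, and treatment is one session (2.7.1, 2.7.2). Patients removed then may have few post-treatment scores, and no model recovers scores that were never taken. A deletion costs a tenth of a single arm, but only one in thirty of a time or frequency level, since each level pools three experimental arms. Finally, SPSS is named only for generating the allocation sequence (2.6), so no argument about analysis software can rest on it. These points reduce the size. They do not justify discarding scores already in hand.

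**Conclusion.** The concern holds in a limited form. Section 2.10 names a method that, as standardly run, throws away collected scores in a trial with 10 patients per arm and expected dropouts. The loss of 4 to 17% of collected scores rests on an assumed 5 to 20% missing the 1-week visit only; the true rate may be lower after one session and a short follow-up.

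Within-arm improvement is overstated only if loss depends on earlier results. The figure of roughly 0.1 to 0.2 SD belongs to the more selective scenarios; rarer or weaker selection gives less. If loss differs between arms, the direction of bias in a comparison is not fixed. The point touches secondary outcomes only. It is worth correcting because the correction is cheap, not because the trial's main result depends on it.

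**What to change.** In 2.10, replace the univariate repeated-measures ANOVA for the four scales with a likelihood-based linear mixed model for repeated measures that uses every available score of every randomised patient. Specify:

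- visit as a category and a stated covariance structure across visits;
- for the comparison with control, arm and arm-by-visit terms;
- for the 3 × 3 experimental part, time, frequency and their interactions with visit, so that the factorial structure is used. A saturated layout of 10 arms by 5 visits would mean 50 means from 100 patients.

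The change costs analysis wording only: no added visits, data or patients. The downside is a slightly more complex model whose validity relies on data missing at random. It recovers scores that were taken and not those that were never taken, so the number of patients contributing at each visit should be reported by arm.
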